**Methods:**

The TeleGDM is a mixed-methods study comprising an exploratory randomized controlled trial (RCT) and a qualitative evaluation using semistructured interviews. It involves women with insulin-treated GDM who are up to 35 weeks gestation. Participating patients (n=100) are recruited face-to-face in outpatient GDM clinics at an outer metropolitan tertiary hospital with a culturally diverse catchment and a regional tertiary hospital. The second group of participants (n=8) comprises Credentialed Diabetes Educator Registered Nurses involved in routine care of the women with GDM at the participating clinics. The RCT involves use of a Web-based patient-controlled personal health record for GDM data sharing between patients and clinicians compared to usual care. Outcomes include service utilization, maternal and fetal outcomes (eg, glycemic control, 2nd and 3rd trimester fetal size, type of delivery, baby birth weight), diabetes self-efficacy, satisfaction, and costs. Semistructured interviews will be used to examine user experiences and acceptability of telemedicine.

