## Introduction

Recent changes to tighten the diagnostic criteria for gestational diabetes mellitus (GDM) [1] mean many more women will be diagnosed with this condition, placing increased demand on clinical services to provide diabetes care. Women with insulin-treated GDM, in particular, often require more intensive follow-up and support for titration of insulin and overall management of GDM [2,3].

The prevalence of GDM is estimated to be 6% to 15% of pregnancies [1,4] dependent on whether the diagnostic criteria set by the International Association of Diabetes and Pregnancy Study Groups (IADPSG) or the Australasian Diabetes in Pregnancy Society (ADIPS) is used. The IADPSG’s revisions in recent years give higher prevalence estimates [1].

Good control of blood glucose level (BGL) in GDM is important to minimize the risk of pregnancy and birth complications associated with the condition. Such complications can include large for gestational age (LGA) babies, macrosomia, increased likelihood of cesarean delivery, preeclampsia, and fetal shoulder dystocia [3-5]. First-line therapy to control hyperglycemia involves dietary modification and physical activity [1,3,6] or oral hypoglycemic agents (OHA) [3]. An insulin regimen is initiated if the OHA therapies are inadequate in optimizing BGL or there is evidence of increased risk of macrosomia [6]. Approximately 50% of women with GDM go on insulin regimen, which requires close monitoring and intensive follow-up for regular insulin titrations to control persisting hyperglycemia [2].

The increasing prevalence of GDM [7-10] and the intensive clinical care needed have implications for the capacity of health care services to provide timely care and the clinical outcomes of such care. There is a need to explore innovative ways to deliver care and support for women with GDM to ease the service burden while not compromising quality of care. This may also potentially deliver cost efficiencies and savings.

In our systematic review [11], telemedicine has emerged as a potentially effective intervention to address service utilization while producing maternal and fetal outcomes similar to or better than usual care.

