### Population, Setting, and Inclusion Criteria

The first group of participants comprises pregnant women diagnosed with GDM who have commenced insulin therapy to control hyperglycemia. These women attended outpatient GDM clinics at two tertiary hospitals between August 30, 2014, and October 30, 2016, inclusive of follow-up. One hospital is in an outer metropolitan region with a catchment population of significant cultural and linguistic diversity. The other is regionally located and serves a population with a rural background. Combined, the two hospitals have approximately 5000 live singleton births annually, and approximately 800 of the pregnancies are affected by GDM.

Women with GDM (patient participant group) are eligible for inclusion if they have a clinical diagnosis of GDM based on the IADPSG criteria following an oral glucose tolerance test [1]. Other eligibility criteria include gestation up to 35 weeks and access to the Internet via a personal computer, smartphone, or tablet. Prepregnancy glucose intolerance, twin pregnancies, GDM not treated with insulin, and other types of diabetes are exclusion factors.

The second group of participants are Credentialed Diabetes Educator Registered Nurses (CDE-RNs) who provide GDM care at the two centers. The CDE-RNs are directly involved in the RCT component of the study and provide care to women with GDM in the course of their usual practice. The number of these clinicians across the two sites is 8; all are requested to complete the clinician assessments for the study.

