### Usual Care (Control)

Usual care refers to clinical GDM care processes currently in practice at the participating hospitals, and this will be the control group. In line with recommended best practice [29,30] diagnostic screening for GDM occurs at 24 to 28 weeks gestation for women with no known history of diabetes or earlier for those considered high risk for GDM. Following diagnosis through to end of pregnancy, ongoing care is provided via a multidisciplinary team of endocrinologists, dietitians, and CDE-RNs. The role of the team is in addition to obstetric care.

From an endocrinology perspective, care involves an initial group counseling and education with a CDE-RN and dietitian covering aspects of GDM self-management. The CDE-RNs provide the pregnant women with free BGL meters from an approved supplier. The meters are individual use and the women purchase their own consumables (ie, test strips and lancing devices). Treatment targets are ≤5.0 mmol/L for preprandial BGL and ≤6.7 mmol/L for 2-hour postprandial BGLs. Insulin is initiated or titrated if BGLs are above target over three successive days. Ongoing face-to-face appointments are scheduled with members of the team as needed until delivery. Appointments generally occur every one to two weeks as determined by the clinicians. Patients on insulin have more frequent reviews especially in the early stages of insulin initiation. Self-management involves keeping a daily paper diary record of GDM self-monitoring data (1 preprandial and 3 postprandial BGLs, insulin dosing, symptoms, and dietary information). The diaries are reviewed by the clinicians at each outpatient clinic. The women also have the option to call the CDE-RNs out of scheduled appointments if BGLs are outside target.

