**Secondary**					
	Clinical measures and satisfaction	Clinician quality of care	Glycemic control	BGL^a^ extraction from OHP^b^; glucometer downloads; patient paper diaries	Enrollment; delivery
			Glycemic stability	Time (days) to BGL stabilization	Between enrollment and delivery
			Insulin adjustments	Time (days) between insulin adjustment	Between enrollment and delivery
			Macrosomia	Fetal ultrasound biometry	2nd (17-22 weeks) and 3rd (>22 wks) trimester
			Diabetes self-efficacy	DES-SF^c^	Baseline; ≥6 weeks
			LGA^d^	Birth weight > 90th percentile	Delivery
			Neonate admission to SCN^e^	Patient medical record	Delivery
			Type of delivery (NVD^f^, LUSCS^g^, other)	Patient medical records	Delivery
			Mother/patient satisfaction with clinical care	CSQ-8^h^	Baseline; ≥6 weeks
					Enrollment; delivery
	Costs	Organization sustainability	Service provider costs	Routine billing administrative data for face-to-face/staff costs; OHP subscriptions	Study exit

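### The fetal biometry outcome is timed by gestation and not by randomization, so the 17-22 week scan, and some later scans, are taken before the women enter the trial

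*Protocol article*

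**What the plan says.** In the secondary block of Table 1, the macrosomia row is measured by fetal ultrasound biometry, with the time point "2nd (17-22 weeks) and 3rd (>22 wks) trimester". The abstract (Methods) names "2nd and 3rd trimester fetal size" among the maternal and fetal outcomes. Data Preparation and Analysis says that the arms will be compared on primary and secondary outcomes and makes no exception for any time point.

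The other relevant statements concern when a woman can enter:

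- Population, Setting, and Inclusion Criteria describes the patients as "pregnant women diagnosed with GDM who have commenced insulin therapy to control hyperglycemia" and requires a "clinical diagnosis of GDM based on the IADPSG criteria following an oral glucose tolerance test". Gestation at entry may be up to 35 weeks; no lower limit is stated.
- Usual Care (Control) says that "diagnostic screening for GDM occurs at 24 to 28 weeks gestation for women with no known history of diabetes". The same sentence makes an exception for women at high risk, who are screened sooner; it gives no gestational week for them.
- The Introduction places insulin after first-line treatment: "An insulin regimen is initiated if the OHA therapies are inadequate in optimizing BGL". Evidence of a raised macrosomia risk is the other trigger it names.

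**The concern.** A randomized comparison is informative about treatment only for measurements made after allocation. Here two gestational windows define the outcome, while entry depends on a chain of events (screening, diagnosis, start of insulin, consent) that for routinely screened women begins at 24 weeks at the earliest. A scan at 17-22 weeks then describes the fetus before the woman was in the trial. The second window opens at 22 weeks and is not tied to entry either.

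The trial's hypothesis is that service use falls without harm to maternal and fetal outcomes. A time point that the intervention cannot influence will tend to show similar arms whatever the intervention does, and so should not count as evidence for that hypothesis.

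**Working it through.** The article gives no figure to reproduce here. The check sets its gestational weeks side by side and then asks how far the early-screening exception could reach.

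**Inputs from the article.** First biometry window 17-22 weeks; second window after 22 weeks (Table 1). Routine screening 24-28 weeks, earlier for high-risk women with no week given (Usual Care). Diagnosis and insulin needed before entry, and entry up to 35 weeks (Population, Setting, and Inclusion Criteria).

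**Step 1: first window against routine screening.** Start of routine screening minus end of first window = 24 - 22 = 2 weeks. Insulin and consent come after screening, so randomization is later still. For every routinely screened woman the 17-22 week scan precedes randomization. This needs no assumption about the case mix.

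**Step 2: second window against entry.**
- A routinely screened woman cannot be randomized before 24 weeks, so a scan between 22 and 24 weeks meets the Table 1 definition and still predates entry.
- A woman enrolled at the 35-week limit could have had a qualifying scan at any point in the preceding 35 - 22 = 13 weeks. For example, a 28-week scan in a woman enrolled at 33 weeks counts under Table 1, yet it was taken 5 weeks before allocation.

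**Step 3: how many women could be exceptions.** Let h be the share of participants who are high risk. Let e be the fraction of those who are screened early, diagnosed, on insulin and randomized by 22 weeks. At most h × e of the sample could have a 17-22 week scan after randomization. It is an upper bound because the scan must also fall after allocation. The article gives neither h nor e, so both are assumed over a range:

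| h (assumed) | h × e at e = 0.1 | at e = 0.5 | at e = 1.0 | e needed for more than half the sample (0.5/h) |
|---|---|---|---|---|
| 0.3 | 0.03 | 0.15 | 0.30 | 1.67, not possible |
| 0.5 | 0.05 | 0.25 | 0.50 | above 1.0, not possible |
| 0.7 | 0.07 | 0.35 | 0.70 | above 0.71 |
| 0.9 | 0.09 | 0.45 | 0.90 | above 0.56 |

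If half the sample or less is high risk, the exceptions cannot be a majority. With a larger high-risk share they could be, but only if most of those women were on insulin and randomized by 22 weeks.

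**Step 4: effect on the comparison.** Analysed alone, a pre-randomization scan has an expected between-arm difference of zero, and what is observed is chance imbalance. If scans were combined in a simple average in which a fraction w predates randomization, a true later effect D would appear as (1 - w) × D + w × 0 = (1 - w) × D. The article gives neither w nor any statement that scans will be combined, so no dilution figure can be derived from it.

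**The case against.** **The early scan may be intended as a baseline.** Other rows of Table 1 pair a first value with a follow-up: glycemic control at enrollment and delivery, and the self-efficacy and satisfaction scales at baseline and from 6 weeks. The biometry row could follow the same pattern, labelled by gestation because scans are scheduled that way. This is plausible. But those rows say enrollment or baseline and this one does not, and the abstract lists second-trimester size as an outcome. If a baseline was meant, the remedy is still to say so. That reading also leaves the second window unanchored.

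**High-risk women are screened earlier.** The high-risk definition used for stratification is broad (several ethnic groups, previous GDM, earlier insulin use), and one site has a diverse catchment. A reader might infer that most participants have the early scan before entry. That is likely, since insulin adds delay after diagnosis, but the article does not establish it, because it gives neither the high-risk share nor gestation at entry. What it does establish is the statement about all routinely screened women.

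**Modelling of serial scans belongs in the SAP.** It does, and its absence is no fault here. The point concerns time points that the article itself fixes and that conflict with its own entry sequence.

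**Fetal size is also measured at birth.** LGA at delivery, and the birth weight named in the abstract, necessarily follow randomization. This stands and limits the harm.

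**Conclusion.** The point holds as a defect in how one secondary outcome is defined. For all routinely screened women the 17-22 week scan precedes randomization, and scans after 22 weeks may do so as well. Such scans carry no information about the intervention. The first conclusion rests only on the weeks stated in the article and on the rule that diagnosis and insulin come before entry.

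Two stronger readings are tempting but unsupported:

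- That the fetal-size effect would be halved. This sets w = 0.5 in the formula above, that is, equal weighting of two scans with every early one taken before entry. The article proposes no such pooling.
- That the trial's conclusion of similar fetal outcomes would be falsely reassuring overall. LGA at delivery remains a valid post-randomization measure of fetal size.

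The primary outcome and the sample size are untouched. The definition should be corrected before analysis, but it does not threaten the trial's main comparison.

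**What to change.** In Table 1 and the analysis text:

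1. Limit the biometry outcome to ultrasounds dated after randomization, for example the last such scan, standardized for gestational age at the scan.
2. Label the 17-22 week scan as baseline and use it as a covariate when it predates randomization. Report it with the baseline characteristics and not as an outcome.
3. Treat any scan dated on or before randomization as pre-entry, whichever window it falls in.

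This changes a definition and not a trial procedure. It needs the scan date and the randomization date for each woman. The article does not state that both are captured, but gestation at the scan is needed anyway to assign a window. The cost is that women with no scan after entry contribute no ultrasound outcome. Their number should be reported by arm, and LGA at delivery still covers fetal size for them.

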**Tertiary**					
	Usage (patients and clinicians)	Technology capability	Clinician system, information and service quality, usage	Modified Canada Health Infoway System And Use Assessment Survey	6 months from beginning of study
			OHP access; volume of data uploaded	Extraction from OHP logs	Study completion

^a^BGL: blood glucose level

^b^OHP: Online Health Portfolio

^c^DES-SF: Diabetes Empowerment Scale–Short Form

^d^LGA: large for gestational age

^e^SCN: special care nursery

^f^NVD: normal vaginal delivery

^g^LUSC: lower uterine segment cesarean section

^h^CSQ-8: Client Satisfaction Questionnaire–8 Item (CSQ-8)

### Qualitative Evaluation

The aim of the qualitative evaluation is to supplement the RCT by exploring patient and clinician acceptance, adoption, and experiences of telemedicine to support care in the management of GDM. A semistructured interview approach is used for both patient and clinician participants. The interview schedule is outlined in Multmedia Appendix 6. Subjects include those who are assigned to the intervention arm of the TeleGDM RCT and the CDE-RNs. A purposive sample of patients will be selected with the aim for up to 15 patients. Since there are only a few clinicians, all CDE-RNs who actively interact with OHP during the RCT will be included. Interviews are conducted by the lead researcher and the questions are open-ended, focusing on gathering interviewee experiences with telehealth-supported GDM management and the technology under use. Clinician interviews are face-to-face while patient interviews are carried out over the phone for the convenience of new mothers. All interviews are audiorecorded digitally for later verbatim transcription.

The interviews will be supplemented with field notes/observations. Notes or written diaries throughout the trial allow for an analysis that provides a narrative account of practice [44]. The narrative adds to the evaluation by highlighting factors in the local setting which may influence the success or failure of the intervention [44,45].

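### Clinician interviews meant to explore adoption are limited to an undefined group of active OHP users, although there are only 8 CDE-RNs and all could be invited

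*Protocol article*

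**What the plan says.** The Qualitative Evaluation section gives the aim of the interviews as "exploring patient and clinician acceptance, adoption, and experiences of telemedicine to support care in the management of GDM". It first describes the interview subjects without any condition on use: "Subjects include those who are assigned to the intervention arm of the TeleGDM RCT and the CDE-RNs". It then observes that the clinicians are few and sets the rule that "all CDE-RNs who actively interact with OHP during the RCT will be included". What counts as active interaction is not stated.

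The size of the clinician group is given under Population, Setting, and Inclusion Criteria: "The number of these clinicians across the two sites is 8; all are requested to complete the clinician assessments for the study".

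Three other sources bear on clinician use of OHP:

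- Table 1 lists, as a tertiary outcome, a clinician survey covering "Clinician system, information and service quality, usage", timed at 6 months from the start of the study.
- Table 1 also takes OHP access and upload volume from "Extraction from OHP logs".
- The Qualitative Evaluation section adds that "The interviews will be supplemented with field notes/observations".

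**The concern.** Adoption is both a topic of the clinician interviews and, through the word actively, the condition for being interviewed. A nurse who never took OHP up, or who left the reviewing to colleagues, is well placed to explain what stands in the way of clinician use, and the rule gives no assurance that she will be heard.

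This matters because the intervention works through these nurses. The Telemedicine (Intervention) section makes them the gatekeepers to the system and rests the approach on clinicians responding promptly to shared data. If the trial showed no reduction in visits, low clinician engagement would be a leading explanation, and the interviews exist to supplement the trial. The Discussion already anticipates favourable clinician views. A rule that may remove the least engaged clinicians makes that expectation harder to contradict.

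**Working it through.** No power, effect size or test is involved. The check is a comparison of statements, with one small calculation.

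**1. Aim against rule.** The aim covers acceptance, adoption and experiences. The rule admits CDE-RNs according to their interaction with OHP. Experiences of use can be studied among users alone. Reasons for not adopting cannot be heard first-hand from a group defined by active use.

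**2. Subjects against rule.** The same section first names the CDE-RNs as subjects without condition, then narrows them to active users. The only reason offered is that there are few of them. A small group is a reason to interview all of it and does not explain leaving some out.

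**3. How far the rule reaches.** Because actively is undefined, the text does not settle borderline cases. A nurse who tried OHP for a while and stopped might count as having interacted during the trial, or might not. A nurse who hardly used it, or never did, most plausibly falls outside.

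**4. Could anyone be inactive?** The Telemedicine (Intervention) section lets clinicians review data when convenient around other duties, with a floor of one review every one to two days on weekdays. The floor concerns how often data are reviewed. It does not say that each CDE-RN must do the reviewing, so some of the 8 could meet it on behalf of the others. The document gives no count of inactive nurses.

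**5. Size.** Let k be the number of CDE-RNs not interviewed because they were not active. The share of the pool missing from the interviews is k/8. The value of k is an assumption:

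- k = 0: 0/8 = 0%, and the rule has no selection effect
- k = 1: 1/8 = 12.5%
- k = 2: 2/8 = 25%
- k = 4: 4/8 = 50%

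**6. What the other sources can supply.**

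- *Survey.* All 8 are asked to complete the clinician assessments. The Data and Outcomes text describes the survey sections used as system and information quality; Table 1 adds service quality and usage. It is scheduled once, at 6 months. The attendance window runs from 30 August 2014 to 30 October 2016, or 26 months. If the study start is taken as the first of these dates, 26 − 6 = 20 months follow the survey, and disengagement in that time would not appear in it.
- *Logs.* These can show that use was low or stopped. They cannot show why.
- *Field notes.* These can record local factors that help or hinder the intervention, but as seen by the observer.

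Each source covers part of the gap. None is a non-user's own open-ended account.

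**The case against.** The strongest reply is that the rule may exclude nobody. The CDE-RNs are described as directly involved in the trial, they are the channel through which OHP reaches the rest of the team, and a minimum review frequency is set. If all 8 use OHP, all 8 are interviewed. This stands: the number excluded is unknown, and a selection effect exists only if it is above zero.

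A second reply is that the interviews are one supplementary component. This also stands, and it rules out several stronger readings that a reader might infer.

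- *That the acceptance and adoption evaluation as a whole leaves out non-adopters.* Only the clinician interviews carry the condition. The assessments are requested of all 8, OHP access is logged, and the field notes are intended to bring out local factors behind success or failure. It would be wrong to say that barriers can be heard only from those who overcame them.
- *That favourable findings are assured.* Active users can report bad experiences, and the direction of any distortion is plausible but not shown.
- *That the bias can be put as an inflated acceptance percentage.* The interviews are open-ended and analysed by theme. No such percentage is planned, and the views of non-users are not known.
- *That the patient interviews share the problem.* Patients are sampled purposively from the intervention arm, and no active-use condition is stated.

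It may also be said that a definition of actively could sit in a fuller protocol, which an article need not repeat. That is fair as to the definition. It does not answer the main point, since the article itself states a rule that depends on use, and any definition of active use would still select on adoption.

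**Conclusion.** The point holds within the clinician interviews. The protocol sets out to explore clinician adoption, names the CDE-RNs as subjects, and then limits interviews to an undefined active subgroup for a reason that supports taking all 8. Each nurse left out removes 12.5% of the clinician pool from the interviews.

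That the findings would lean favourable rests on two assumptions: that at least one CDE-RN is inactive, and that inactive nurses tend to hold less favourable views than active ones. Both are plausible and neither is established by the document. The survey, logs and field notes reduce the loss without removing it. No outcome of the randomized comparison is affected. The change is worth making because it costs little and the missing account cannot be recovered from the other sources.

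**What to change.** In the Qualitative Evaluation section, replace the inclusion rule with: *All 8 CDE-RNs at the two sites are invited to interview regardless of their level of OHP use.* Add that each interviewee will be described by OHP log activity, and that any CDE-RN not interviewed will be reported with the reason.

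This brings the rule into line with the section's own statement of subjects and with the request that all 8 complete the clinician assessments. It also removes the need to define actively. No change to the patient sample is called for.

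The cost is at most a few additional interviews, from a pool of 8, by the lead researcher who already conducts them. If every CDE-RN turns out to be an active user, the number of interviews does not change.
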